**Figure 2 F2:**
[figure not shown]
Flow diagram summarising the procedures each participating patient will undergo in this study.

### Sample size justification

It is estimated that a sample size of 586 patients (293 per arm, allowing 20% loss to follow-up) is needed for 90% power to detect a standardised effect size of 0.3 (equivalent to a difference from baseline to 12-month follow-up in ACT score of 1.05), assuming an SD of 3.5.^41^ This gives a total of 234 patients per arm with completed follow-up data. In the previous feasibility study, we had a 10% response rate in the recruiting survey and a recruitment rate (ie, proportion of survey respondents consenting to and receiving the intervention) of 9.8%. Assuming response and recruitment rates are similar in the RCT, the survey will need to be circulated to just over 59 000 patients (see figure 1 for detailed calculation).

### Data management

An online database will be designed on REDCap by the Pragmatic Clinical Trials Unit (PCTU) at Queen Mary University of London (QMUL), for study data capture and storage. Online copies of the recruiting survey, consent forms and case report forms for collecting baseline and follow-up measures will be stored in the online database. Data related to participants’ online activity in the ALUK OHC will be transferred by HealthUnlocked directly into the Data Safe Haven (DSH) platform (ie, QMUL’s technical solution for storing, transferring and analysing research information containing highly confidential data). The DSH will also be used to transfer the email addresses of patients having received the intervention to HealthUnlocked, so that their activity can subsequently be identified. Data extracted from clinical records will be stored on the DSH. Demographic data from HCPs participating in the exit one-to-one interviews will be pseudonymised and stored on the DSH. Any hard copies of demographic forms will be stored separately inside locked filing cabinets, within a locked office at QMUL. Original audio recordings from exit interviews will be downloaded and stored, along with original transcripts, on the DSH at QMUL. Edited versions of the transcripts, pseudonymised and with all identifiers removed, will be stored on QMUL’s secure server (SharePoint). Only members of the research team will have access to study data, which will be retained in accordance with QMUL policies. Processing and analysis of data will be undertaken solely on QMUL password-protected computers.

### Data analysis

All analyses of study data will be carried out collectively by the research team with extensive input from staff from the PCTU when it comes to statistical tests and health economic processes. Social network analysis of participants’ engagement with the OHC will be conducted using Python.^42^ Qualitative analyses will be facilitated by NVivo software.^43^ R^44^ and Stata^45^ will be used to carry out quantitative analyses.

### Quantitative analyses

Team members involved in developing the statistical analysis plan will be blinded to allocation of codes being provided to the analysis. The mean, median, range and SD for ACT at baseline and all follow-up time points will be presented along with the same for 8-item Patient Health Questionnaire depression scale, EuroQol 5-Dimensions 5-Level version (EQ-5D-5L), Generalised Anxiety Disorder 7-item scale, Medication Adherence Rating Scale, self-efficacy scores, number of asthma exacerbations and primary and secondary care health service utilisation over the last 12 months (at time points where these are collected).

The main analysis of the primary outcome will draw on a linear regression approach to compare the ACT at the final (12-month) follow-up point in the two groups, adjusting for baseline value, including general practice as a random effect in a mixed model. We will also include a repeat measures analysis (simultaneously analysing ACT score at each time point) to complement the primary analysis, again using a mixed-model procedure. In addition, we will carry out a per-protocol analysis, including in the treatment arm only those participants who used the digital intervention at least once in each of three consecutive months.

Similarly to the main analysis, we will compare 12-month data for the other outcomes listed above, adjusting for baseline using a mixed modelling approach. The exact nature of a given analysis will depend on the outcome variable (eg, continuous, binary, ordinal, categorical), allowing for GP-level clustering in the data.

Data related to healthcare use from healthcare records (eg, healthcare needs, including primary care visits, investigations, asthma medication, asthma exacerbations and hospital admissions) will also be analysed through descriptive and inferential statistics and assessed against baseline and follow-up measures. For example, regression models will also be employed to associate participant-reported outcomes and data in relation to primary/secondary care use, thereby further contributing to evidence regarding the effectiveness of the intervention.

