### Participants

Approximately 600 patients with uncontrolled asthma (ie, an asthma control test (ACT) score of <20) from 50 to 70 general practices will be recruited via an online survey, sent to approximately 60 000 patients on the asthma register.

To participate in the study, participants will need to:

Be adults (aged 18 years and above) on the asthma register, who have expressed their interest in digital social interventions in the recruitment survey;Report uncontrolled asthma in the recruitment survey;Be able to provide informed consent, as determined by the HCP carrying out the study appointment.

Exclusion criteria

Patients who are:

Already members of the ALUK asthma OHC or other asthma OHCs/Facebook groups (general use of social media will not prevent participation).Receiving palliative care or with very limited life expectancy (<12 months).Receiving institutional long-term care (receiving total care in residential homes or living in nursing homes).Considered unsuitable to take part in the study by their general practitioner (GP)/nurses.

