### Study procedures

#### Recruiting survey

The survey includes a screening section, asking patients to confirm they have an asthma diagnosis and are over 18 years, followed by questions establishing their eligibility for the trial (ACT questionnaire, membership of online asthma forums/Facebook groups and interest in taking part in the trial), with an additional section about support with managing their asthma. Eligible respondents will be asked to provide their contact details. Survey and study data will be recorded using Research Electronic Data Capture (REDCap) software, a secure application for designing and managing online surveys and databases. Completion of the recruiting survey is anticipated to take <5 min (see online supplemental material 1 for a copy of the recruiting survey).

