### Outcomes and measures

Twelve months following the face-to-face appointment, all participating patients will receive a text message and/or email with a link to an online survey collecting follow-up measures (up to three reminders will be sent). In addition, patients who have consented to receiving regular contact will be telephoned by a member of the research team every 3 months during the 12-month follow-up period to collect data on asthma control, quality of life and care utilisation.

The primary outcome of interest will be ACT score collected every 3 months for 12 months following the face-to-face appointment (adjusted for baseline value in the analysis). Secondary outcomes will include variables related to the overall health and well-being of the patient, as well as associated care utilisation (table 1). In addition to outcomes self-reported by patients (table 1), non-self-reported outcome variables will be obtained (table 2), depending on data availability and consent for access to healthcare records.

**Table 1 T1:** Outcomes self-reported by participants

Domain	Outcome	Measure	Baseline*	3 months†	6 months†	9 months†	12 months‡
Clinical factors	Control of asthma§	ACT questionnaire	X	X	X	X	X
	Asthma exacerbations over last 3 months	Bespoke question	X	X	X	X	X
	Adherence to medications	MARS-10 questionnaire	X				X
Quality of life	Health-related quality of life	EQ-5D-5L questionnaire	X	X	X	X	X
Healthcare use and time off work (economic factors)	Primary and secondary care use over last 3 months	Bespoke question	X	X	X	X	X
	Time off work to seek care and/or due to asthma over last 3 months	Bespoke question	X	X	X	X	X
Psychosocial factors	Depression	PHQ-8 questionnaire	X				X
	Anxiety	GAD-7 questionnaire	X				X
	Self-efficacy	General Self-Efficacy Scale	X				X
	Smoking status	Bespoke question	X				X
OHC use factors (only related to intervention arm participants)	Amount and type (passive vs active) of OHC engagement	Bespoke question					X
Internet use for health support	eHealth literacy	eHealth Literacy Scale	X				
	Interest in and appropriateness of digital social interventions in primary care	Bespoke question	X				

* At the time of the study-related face-to-face appointment.

† Interim follow-up at 3, 6 and 9 months following the face-to-face appointment, data collected over the telephone by the research team.

‡ Final follow-up survey 12 months following the face-to-face appointment, survey self-completed by participants.

§ Primary outcome.

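### The primary model names one baseline ACT although every participant has two pre-randomisation scores; adding the second is a small, free gain in precision

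*Protocol article*

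**What the plan says.** Two ACT scores precede randomisation.

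- **Recruiting survey.** This section describes questions "establishing their eligibility for the trial (ACT questionnaire, membership of online asthma forums/Facebook groups" and interest in the trial. Participants makes the result a condition of entry: "Report uncontrolled asthma in the recruitment survey", with uncontrolled meaning an ACT below 20. Survey and study data are both recorded in REDCap.
- **Appointment.** Table 1 (Outcomes and measures) schedules an ACT at baseline, and its footnote defines baseline as "At the time of the study-related face-to-face appointment". Randomisation takes place at that same visit, after baseline collection.

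The main analysis will "compare the ACT at the final (12-month) follow-up point in the two groups, adjusting for baseline value". Outcomes and measures also refers to the baseline value in the singular. No analytic role is stated for the survey score.

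Randomisation stratifies on ACT in two groups, below 12 and 12 to 19, without saying which of the two scores is used. A statistical analysis plan, to be signed before database lock, will give more detail.

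**The concern.** A single ACT reading is a noisy measure of a patient's underlying asthma control. Two readings on separate occasions usually predict a later score better than one. The survey score exists for every randomised participant, because nobody can enter without it, so using it should cost no one from the model. It was measured before allocation, so adjusting for it does not bias the treatment comparison. Selecting on survey ACT below 20 narrows its range and weakens it as a predictor, but does not remove its information.

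Mode of collection gives a further reason, though only by inference. The survey ACT and the 12-month ACT are both completed online, whereas the appointment score is recorded by the health professional.

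At stake is the standard error of the primary contrast, which may be slightly larger than the data already held would allow.

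**Working it through.** **1. The plan's own sample size.** Inputs come from Sample size justification. The target there is a 1.05-point ACT difference with SD 3.5, that is a standardised effect of 0.3, at 90% power. The total is given as "586 patients (293 per arm, allowing 20% loss to follow-up". The significance level is not stated; I assume 0.05 two-sided.

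- Per arm: n = 2 × (1.960 + 1.282)² × (3.5/1.05)² = 2 × 10.51 × 11.11 = 233.5, so 234.
- With 20% loss: 234/0.8 = 292.5, so 293 per arm and 586 in total.
- Power with 234 per arm: 90.06%.

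The stated figures reproduce, and no baseline correlation enters them. Any useful baseline adjustment therefore takes power above 90%.

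**2. Gain without selection.** Let r be the correlation of each pre-randomisation ACT with the 12-month ACT, and s the correlation between the two. Neither is in the article.

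- Residual variance with one score: 1 − r².
- With both: 1 − 2r²/(1 + s).
- Proportional cut: r²(1 − s) / [(1 + s)(1 − r²)].

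| r | s | One score | Both scores | Cut | Power, 234 per arm |
|---|---|---|---|---|---|
| 0.4 | 0.9 | 0.840 | 0.832 | 1.0% | 94.3% to 94.5% |
| 0.5 | 0.8 | 0.750 | 0.722 | 3.7% | 96.3% to 96.8% |
| 0.5 | 0.5 | 0.750 | 0.667 | 11.1% | 96.3% to 97.8% |

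These ignore the entry criterion, which truncates the survey score.

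**3. Gain with selection on survey ACT below 20.** I simulated three jointly normal scores, rounded and limited to 5 to 25, and kept those with survey ACT below 20. Assumed population mean/SD: 17/4.5, 18.5/4.25 and 20/4. I took s = 0.5, 0.6, 0.7, 0.8, 0.9 and r = 0.4, 0.5, 0.6, which gives 45 scenarios. Variance ratios were applied to SD 3.5 with 234 per arm.

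| Quantity | Range over the 45 scenarios |
|---|---|
| Cut in residual variance from adding survey ACT | 0.7% to 11.5% (27 of 45 between 2% and 6%) |
| Same, with a survey-ACT below-12 indicator already in the model | 0.6% to 6.3% |
| Power with the appointment ACT only | 91.8% to 96.9% |
| Rise in power | 0.2 to 1.4 percentage points |

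For a middle case (mean 18.5, SD 4.25, s = 0.7, r = 0.5) the cut is 3.5%. Power goes from 93.9% to 94.6%, and the 95% confidence interval half-width from 0.588 to 0.577 ACT points. A 3.5% cut is worth 468 × (1/0.965 − 1) ≈ 17 completers on the planned 468.

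The largest gains need the two early scores to correlate less with each other than each does with a score a year later (s = 0.5, r = 0.6). That is the least plausible corner of the grid.

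**The case against.** The strongest reply is that nothing here is wrong. Analysis of covariance on one baseline score is standard and unbiased, and the trial exceeds its stated power without the second score. That stands: this is an efficiency point, not an error.

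A second reply is that the covariate list belongs in the statistical analysis plan, and that the article sketches an approach without saying only one covariate is allowed. This stands in part. A reader might infer that the survey score is used as an entry filter and then thrown away, but no section says so and the analysis plan could still include it. Even so, the article does name a single baseline value, so the addition needs to be written down.

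A third is that the survey score may already enter through stratification. The upper limit of 19 fits the survey score, since the article guarantees a score below 20 only there. This is a reading, not a stated fact. If it is right and the strata are in the model, the remaining gain falls to about 0.5% to 6%.

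Finally, the Introduction stresses delivering the intervention soon after recruitment. That suggests a short gap between the two scores, a high correlation between them, and a gain towards the low end.

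**Conclusion.** The point holds as a minor missed efficiency. Two pre-randomisation ACT scores are collected and the primary model names one. Adding the other cuts residual variance by about 1% to 11%, mostly 2% to 6%, or about 0.5% to 6% with a survey-based stratum already in the model. The rise in power is about 0.2 to 1.4 percentage points. All of these figures rest on assumed correlations and score distributions; only the direction follows from the design.

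A reader might infer that the trial is underpowered or its primary comparison flawed. The article does not support that: the stated N reproduces without any baseline adjustment, and the planned model is valid. No conclusion of the trial is likely to turn on this change.

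**What to change.** In Quantitative analyses and the statistical analysis plan, before database lock, specify the primary model as 12-month ACT on arm, appointment ACT and recruiting-survey ACT, the two scores as separate linear covariates, with practice as a random effect. Separate terms suit a truncated survey score better than a simple mean of the two. Use the same two covariates in the repeated-measures model.

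State which ACT defines the randomisation stratum. Confirm that each survey record is linked to the trial identifier in REDCap; this may already be so, since both sets of data are held there.

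Cost: a sentence or two of text, one degree of freedom, and at most one record linkage. No new data and no burden on participants. Low priority, but the choice should be fixed in advance, because adding a covariate after results are seen would not be credible.

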### Health economic assessment

The health economic assessment will include within-trial and long-term cost-effectiveness analyses (likely a Markov model), which will be informed by the within-trial analysis, of OHCs’ enhanced management versus current standard of asthma management in UK primary care. The analysis will be conducted from the perspectives of both health and social care services and wider society, adhering to the National Institute for Health and Care Excellence guide to the methods of technology appraisal,^46^ to ensure that study findings are informative for national-level policy considerations.

As part of the health economic assessment, we will assess the resource requirements and costs for development, moderation, governance and clinical oversight of OHCs. Costs of OHCs, healthcare and other resource use will be evaluated using nationally representative unit costs of primary and secondary healthcare services.^47^ Participants’ quality of life and utility scores will be used in a regression model to examine the relationship between baseline characteristics, asthma control (ACT score) and adverse events during the study, with their impact on quality of life and utility. The within-trial cost-effectiveness will be assessed as incremental cost per quality-adjusted life year (QALY) gained, with QALYs assessed in two ways. First, study data will be used to directly evaluate individual participants’ QALYs over the duration of the study (primary analysis). Second, the quality-of-life regression model will be used to predict quality of life of participants during the study, to increase the precision in the analysis (secondary analysis).

The long-term cost-effectiveness of the OHCs will be evaluated using a long-term asthma model. The quality-of-life regression model will be used to project quality of life associated with different patients and model states in the model. This model, together with trial participants’ characteristics and effects of OHCs on the primary outcome, the ACT score and the adverse events during the study will be used to evaluate long-term cost-effectiveness of OHC in terms of incremental cost per QALY.

Efforts will be made to minimise omissions in prospectively collected data during the study (eg, ACT score, asthma exacerbations, EQ-5D-5L, some resource use). The impact of any missing data on health outcomes and costs will be addressed using appropriate methods depending on pattern and proportion of missing data and type of outcome measure. It is expected that linked routinely collected health data (eg, asthma exacerbations) may alleviate some missing data issues. Results will be presented as incremental cost-effectiveness ratios. The non-parametric bootstrap approach will be used to evaluate the uncertainty in cost-effectiveness while capturing the correlation between health outcomes and costs at individual level and cost-effectiveness acceptability curves will be used to summarise the uncertainty across thresholds of willingness to pay from £0 to 50 000 per QALY gained.

Both the statistical and health economic elements of the quantitative analysis will be described in more detail in a statistical analysis plan and health economic analysis plan, respectively, both of which will be completed and signed before the study database is formally locked.

### Analysis of qualitative data from exit interviews

Audio-recordings from the exit interviews will be transcribed *verbatim* by a professional transcribing agency and analysed thematically using the six stages of reflexive thematic analysis by Braun and Clarke.^48^ Both inductive and deductive approaches will be employed in thematic analysis coding. Coding schemes as well as themes and subthemes will be informed by social support theory (as framed by Dennis^49^) and will aim to synthesise and interpret experiences of the intervention’s delivery and participation in the study in general. Attention will be paid to identifying ‘direct’ effects (ie, directly impacting health-related outcomes), ‘buffering’ effects (ie, reducing the detrimental influence of stressors on health) and ‘mediating’ effects (ie, indirectly influencing health via cognitions, emotions and behaviours) in the interview data. These represent the main ‘effect models’ (ie, mechanisms resulting in beneficial outcomes) underpinning peer support interventions, as outlined in Dennis’s model.

### Analysis of OHC activity data

Data related to participant activity in the ALUK OHC will be analysed through qualitative (eg, thematic and content analysis) and quantitative techniques (eg, descriptive and inferential statistics) as well as network analysis methods (eg, network measures and visualisations) and sentiment analysis (eg, sentiment labelling and tracking sentiment dynamics). Analyses of this data will aim to generate meaningful themes (eg, themes related to self-management support and patterns of online communication leading to improved sentiment and self-management behaviours); quantify online peer support received versus that offered within the OHC environment; develop visual maps of the network containing key users including the participants and of information diffusion within that network and understand correlations between engagement with other peers and outcomes. For thematic analysis, the method of Braun and Clarke^48^ will be used and both inductive and deductive approaches to coding will be pursued. Should certain themes related to self-management behaviours be identified, the frequency of these concepts will be further explored/quantified in the whole data set via conceptual forms of content analysis. Theoretical mediators of the intervention effect will also be measured. OHC activity data will be linked to health-related data and Dennis’s conceptual model will be employed to link improvements in patient outcomes to theoretical mechanisms.^49^ For the network analysis, dynamic networks will be constructed and visualised to show the evolution of users’ activities in the OHC. Key network properties will be investigated using traditional centrality measures. In addition, ego-centred networks will be constructed, and Burt’s measures of structural holes and brokerage^50^ will be applied to these networks to provide in-depth understanding of users’ social capital. Sentiment analysis will explore how interactions, particularly with superusers, drive sentiment shifts, improved emotional well-being and behavioural changes, helping to uncover potential causal links between engagement patterns and users’ health-related outcomes. Finally, regression analyses will be conducted to unveil the correlation between network properties and users’ health-related outcomes.

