#### Intervention arm

After the collection of baseline measures, the face-to-face appointment with participants in the intervention arm will involve:

Signposting to the ALUK asthma OHC by offering a ‘tour’ of the OHC and explaining the different sections of the website.An introduction to norms and values for passive (just reading) and active (writing OHC posts) participation.Explaining the differences between posting publicly and privately (public posts are shared, according to HealthUnlocked terms and conditions, with third parties whereas private messages can be sent via the chat function and are not shared).Motivation for engagement with the OHC to seek and offer self-management information and support, by emphasising that the OHC could be used ad hoc (eg, when feeling unwell or when emotional support is needed).Problem solving with respect to any difficulties/concerns.Signing patients up to the OHC, by explaining terms and conditions of HealthUnlocked.

To sign up participants, HCPs will ask them to use their own mobile phone/other electronic device and access a study-specific landing page provided by HealthUnlocked, outlining the consenting process to the OHC and containing a privacy notice. This allows easy onboarding by default opting out participants from any sharing of collected data with third parties. Participants will need to provide their email address and will be invited to choose an anonymous username. Participants’ email addresses will not be visible within the OHC.

Participants will leave the face-to-face appointment with a card with a QR code link to the ALUK OHC on one side and to the study website/contact details on the other side and a reminder of their username and password (data not recorded for the study). Once logged into the OHC, participants will have the opportunity to change their username/password as well as any other settings in their account (eg, opting in for receiving HealthUnlocked emails).

Depending on the availability of resources, monthly text messages might be sent to participants who have consented, reminding them to engage with the OHC.

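### The forum-activity analyses are worded as uncovering causal links, but engagement is not randomised and use is encouraged when unwell; they support associations only

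*Protocol article*

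**What the plan says.** Under Analysis of OHC activity data, the Protocol article states: "Sentiment analysis will explore how interactions, particularly with superusers, drive sentiment shifts, improved emotional well-being and behavioural changes". The same sentence describes this as "helping to uncover potential causal links between engagement patterns" and health outcomes. The section also plans to tie improved outcomes to theoretical mechanisms, and closes with a more cautious sentence: "regression analyses will be conducted to unveil the correlation between network properties and users’ health-related outcomes".

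Under Intervention arm, the health professional motivates participants by stressing that "the OHC could be used ad hoc (eg, when feeling unwell or when emotional support is needed".

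Tables 1 and 2 restrict engagement data to the intervention arm. Table 2 lists the time of each public post, together with platform metrics such as logins. ACT is scheduled at baseline and at 3, 6, 9 and 12 months. The interim values come from consenting patients, who are "telephoned by a member of the research team every 3 months during the 12-month follow-up period".

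**The concern.** Asthma control fluctuates. If some participants turn to the forum when control is poor, use and poor control will be associated even if the forum does nothing. A helpful forum could then look useless or harmful. The opposite pattern is also plausible: people who are well, organised and motivated may engage more, and an ineffective forum could look helpful. The documents do not show which pattern dominates.

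The trial thus encourages an exposure that depends on the outcome, and then describes the exposure-outcome relation in language that runs from exposure to outcome. At stake is the explanatory conclusion about how engagement works, which could be quoted as a causal result of a randomised trial although no randomised contrast lies behind it.

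**Working it through.** **The plan's own figure.** The documents give no figure for the engagement analyses, so the sample size is reproduced to fix the number of patients. Inputs from Sample size justification: difference 1.05, SD 3.5, power 90%, loss 20%. Two-sided 5% significance is assumed.

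- Standardised effect: 1.05 / 3.5 = 0.30.
- Per arm: 2 × (1.960 + 1.282)² / 0.30² ≈ 233.5, so 234.
- With 20% loss: 234 / 0.8 = 292.5, so 293 per arm and 586 in total.

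This agrees with the plan. The engagement analyses would have about 234 patients.

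**Simulation with no effect of use on control.** Assumptions, none of them from the documents except n = 234 and SD 3.5:

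- Control is half stable trait and half a monthly autoregressive process (correlation 0.7).
- Monthly use is Poisson, with log rate rising by g per SD of worse current control. A g of 0.2, 0.3, 0.5 or 0.7 means exp(g) − 1 = 22%, 35%, 65% or 101% more use.
- Use also varies between patients (log-SD 0.8).
- The 12-month ACT is regressed on log total use; slopes are ACT points per SD of use; 1,500 runs per setting.

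| g | Unadjusted slope | Significant | Baseline-adjusted slope | Significant |
|---|---|---|---|---|
| 0 | 0.00 | 4.9% | 0.00 | 4.5% |
| 0.2 | −0.50 | 59% | −0.27 | 28% |
| 0.3 | −0.74 | 91% | −0.41 | 54% |
| 0.5 | −1.15 | 100% | −0.67 | 91% |
| 0.7 | −1.49 | 100% | −0.93 | 99.5% |

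Adjusting for baseline ACT shrinks the artefact but does not remove it.

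**Sensitivity to the assumptions (baseline-adjusted).** With monthly correlation 0.6 and no extra variation in use between patients, 36% to 100% of runs were significant for g from 0.1 to 0.3. With between-patient log-SD 0.5 the figure was 62% at g = 0.3; with log-SD 1.0 it was 17% to 20%. In a quarterly version with log-SD 0.8 and g = 0.1 it was 10% to 12%. The artefact is therefore modest when the gradient is weak or use is very uneven, and near certain when the gradient is steep and use is even.

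**Which ACT values to adjust for.** One option is to condition on ACT up to and including the value at the end of the engagement period. In the no-effect simulations this looks clean: relating use in months 1 to 9 to 12-month ACT, given ACT at 0, 3, 6 and 9 months, gave slopes of −0.01 to −0.02 points and 4.1% to 5.6% significant for g from 0.2 to 0.7. But those ACT values are partly measured after the use and carry any benefit of it. The interval version of this model was run with a true benefit and no reverse causation (each use raising control by 0.1 to 0.2 SD and fading by a monthly factor of 0.6 or 0.3). It gave slopes of −0.02 to −0.06 SD, significant in 11% to 57% of runs, while the simple cumulative regression gave the correct sign (+0.08 to +0.10 SD). Conditioning on later ACT can hide or reverse a real benefit.

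Adjusting only for ACT at the start of the interval and earlier avoids that problem. In the no-effect setting the spurious slope fell to about a third to a half, on a per-interval rather than cumulative scale. With more uneven use, or with use counted right up to the outcome call, the fall was smaller or absent. Significant results stayed more frequent than 5%.

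**The case against.** The strongest reply is that the text is more careful than the concern suggests. The causal phrase is hedged twice and belongs to the sentiment analysis; the regression sentence promises only "regression analyses will be conducted to unveil the correlation between network properties" and outcomes. Time order and covariates are model details that a condensed article may leave to the statistical analysis plan, and the section does mention dynamic networks and the tracking of sentiment over time. All this stands. The absence of a specified adjustment set is therefore not the criticism. What remains is the stated inferential aim, including the verb *drive*, which these data cannot support.

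A reader might infer several stronger points that the documents do not bear out:

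- *That participants are instructed to use the forum when ill.* The text says it could be used that way, as an example.
- *That all the activity analyses claim causation.* Only the sentiment sentence does so openly.
- *That a strong spurious association is to be expected.* It is possible; its size rests on a gradient that is not given.
- *That the bias has a known sign.* Motivated users could reverse it.
- *That the trial's main result is compromised.* The randomised ACT comparison does not use engagement.

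**Conclusion.** The point holds as one about interpretation. Engagement is not randomised, poor control can prompt its use, and the wording reads the resulting association towards cause. Under no true effect, a baseline-adjusted regression on cumulative use was significant in roughly 20% to 100% of simulated trials of 234 patients, and in about 10% where a weak gradient was combined with uneven use. These figures rest on assumed gradients, an assumed pattern of fluctuation in control and an assumed spread of use, and on a regression that the article does not itself specify. They show that the artefact can be large, not that it will be. The affected analyses are secondary and explanatory.

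**What to change.** 1. In Analysis of OHC activity data, replace *drive* with *are associated with* and *potential causal links* with *associations*. State that reverse causation is expected because use is encouraged when patients feel unwell, and keep causal statements for the randomised comparison.
2. Where engagement is related to ACT, use dated engagement and adjust for ACT at the start of the interval and earlier. Do not adjust for ACT measured after that engagement.
3. State that this reduces but does not remove reverse causation, and leaves confounding by motivation, so the results stay exploratory.

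**Cost:** a more modest claim, changed wording and a little programming. Posts carry times. The per-protocol rule (use in each of three consecutive months) implies that other use is dated too, but this should be confirmed with the platform, because Table 2 lists those metrics only at 12 months. The interval analysis covers only patients who take the 3-monthly calls.
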